#### Type of analysis

The primary efficacy comparison is the comparison of the proportion of responders in the per-protocol population, where a responder is defined as ≥ 1-point improvement in the mean weekly peak pain measured with the PI-NRS (maximum pain) during the 12-week treatment period after first study drug infusion compared to baseline, using Kaplan-Meier curves (log rank test). The following sensitivity analyses will be performed. The primary efficacy analysis will be repeated in the per-protocol population using a more strict definition of a responder: a “responder of ≥ 2 points” is defined as ≥ 2 points improvement in the PI-NRS at the last evaluation after the first study drug infusion during the blinded 12-week treatment period compared to baseline.

In the intention-to-treat (ITT) population, the following additional sensitivity analyses will be performed: any subject who drops out with at least the week 6 PI-NRS assessment with their last mean weakly peak pain on the PI-NRS will be carried forward. A subject dropping out before the week 6 PI-NRS assessment or any subject with no baseline PI-NRS will be counted as a nonresponder independent of the last PI-NRS. Furthermore, in the ITT population, the following sensitivity analyses will be performed. The analysis will be repeated using a more strict definition of a responder: a “responder of ≥ 2 points” is defined as ≥ 2 points improvement in the PI-NRS at the last evaluation following the first study drug infusion during the blinded 12-week-treatment period compared to baseline. Subjects with no baseline or no postbaseline PI-NRS assessment will be counted as a nonresponder in this analysis.

When values are missing, we will use multiple imputation based on a regression method, using SPSS (IBM Corp. Released 2015. IBM SPSS Statistics for Macintosh, Version 22.0. Armonk, NY: IBM Corp) or Stata (StataCorp. 2013. Stata Statistical Software: Release 13. College Station, TX: StataCorp LP).

The differences between the per-protocol analyses and the ITT analyses will give a good impression of the bias that might occur in the study. Comparing these two methods, we can make a clear picture of the two populations and can investigate the true effect of IVIg in the most reliable way.

The secondary efficacy variables will be tested for treatment group differences by analyses of covariance (ANCOVAs) with the baseline measurement as the covariate and the difference of the last post-baseline measurement in the treatment period relative to baseline as an independent variable (treatment group as fixed factor). If no postbaseline measurement is documented, the baseline measurement will be used as the last postbaseline measurement. This analysis is an endpoint analysis using the “last observation carried forward” (LOCF) approach.

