## Methods/design

### Objectives

The primary objective of the study is to evaluate the efficacy of IVIg treatment for pain alleviation compared to placebo in patients with skin-biopsy-proven I-SFN.

Secondary objectives are to assess the effect of IVIg on pain intensity, pain qualities, and other small fiber neuropathy-related complaints and daily and social functioning, as well as quality of life. In addition, safety features of IVIg therapy in SFN will be evaluated.

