#### Exclusion criteria

Subjects presenting with any of the following will not be included in the study:Predominant clinical picture of large nerve fiber involvement (i.e., weakness, loss of vibration sense, and hyporeflexia or areflexia)Treatment with IVIg or any other immunomodulatory/immunosuppressive agents (e.g., steroids) within the last 12 weeks prior to the date of informed consentAn underlying cause of SFN (diabetes, *SCN9A/SCN10A/SCN11A* mutations, hypothyroidism, renal failure, vitamin B12 deficiency, monoclonal gammopathy, alcohol abuse (more than 5 IU/day), malignancies, or drugs that cause neuropathy (e.g., chemotherapy, amiodarone, and propafenone))History of anaphylaxis or severe systemic response to immunoglobulin or with a blood productCardiac insufficiency (NYHA III/IV), cardiomyopathy, significant cardiac dysrhythmia requiring treatment, unstable or advanced ischemic heart disease, history of congestive heart failure, or severe hypertension (diastolic blood pressure > 120 mmHg or systolic > 170 mmHg)Known hyperviscosity, history of renal insufficiency or high serum creatinine levels (MDRD < 30), selective IgA deficiency, or hypercoagulable state.Conditions whose symptoms and effects could alter protein catabolism and/or IgG utilization (e.g., protein-losing enteropathies, or nephrotic syndrome).Females who are pregnant, breast-feeding, or, if of childbearing potential, unwilling to practice adequate contraception throughout the studyMentally challenged adult subjects unable to give independent informed consentPatients using pain medication that has changed in the 30 days prior to randomization (unchanged pain medication is allowed, provided dosages stay equal during the study)

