### Statistical analysis

#### Sample size

A 1-point change on the PI-NRS compared to baseline is considered as the minimum clinically important difference (MCID), according to the unified rule of ½ x SD and recommendations given by the IMMPACT group [38, 43]. In the placebo group, we assume a response rate of approximately 25 % in the placebo-treated group, based on a meta-analysis of the placebo effect in pain studies in which the effect varied from 7 to 37 %, and where 16 % of the patients had a pain reduction of 50 % [32]. In the IVIg treated group, we assume a response rate of approximately 60 % based on the IMMPACT criteria [38].

Fixing a one-sided alpha at 5 %, a sample size of 24 patients per treatment group would be required to show efficacy with 80 % power and an effect size of 60 % between the two groups (chi-square test). Accounting for a dropout rate of approximately 20 % (six patients), 30 subjects per treatment group will be included in this study.

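### The primary superiority comparison is fixed in the per-protocol population with intention-to-treat only as sensitivity analysis, so the one-sided 5 % error rate is not assured and the direction of any bias is unknown

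*Protocol article*

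**What the plan says.** The objective is to "evaluate the efficacy of IVIg treatment for pain alleviation compared to placebo" (Objectives). No non-inferiority margin is given, so this is a superiority question.

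Under Type of analysis, the article fixes the main analysis set: "The primary efficacy comparison is the comparison of the proportion of responders in the per-protocol population". ITT follows in a lesser role: "In the intention-to-treat (ITT) population, the following additional sensitivity analyses will be performed". In that ITT analysis, a patient who drops out after the week 6 assessment has the last value carried forward. A patient who drops out before week 6 "will be counted as a nonresponder independent of the last PI-NRS". Multiple imputation is also named for missing values, without saying to which analysis set it applies.

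The same section defends having both sets: "The differences between the per-protocol analyses and the ITT analyses will give a good impression of the bias that might occur in the study". It adds that comparing the two is the most reliable route to the true effect.

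The sample size section sets the error rate ("Fixing a one-sided alpha at 5" %) and the number needed ("a sample size of 24 patients per treatment group would be required to show efficacy with 80" % power), then adds six patients per arm for a dropout rate of about 20 %, giving 30 per arm.

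**The concern.** Randomisation makes the two arms comparable as allocated. A per-protocol set departs from that, because membership is decided by what happens after allocation. The article does not define its set, but it names events that such a set might use:

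- drop-out, planned at about 20 %;
- infusions below the calculated volume, for which reasons are recorded (Compliance);
- changes in analgesics, since "unchanged pain medication is allowed, provided dosages stay equal during the study" (Exclusion criteria).

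Each can depend on tolerability or on pain, and so on treatment and on outcome. If it does, the responder proportions no longer compare the randomised groups, and the nominal 5 % error rate need not hold. This is the trial's only primary claim, and the Discussion expects positive findings to lead to a new treatment option.

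The stated safeguard does not repair this. The per-protocol and ITT analyses may differ in how they handle dropouts as well as in whom they include. A gap between them can therefore mix two causes. Agreement does not show absence of bias either, since both can be off in the same direction. No rule says which result prevails if they disagree, so by default the per-protocol result carries the claim.

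**Working it through.** **1. Inputs (Sample size section).** Responder rates 25 % (placebo) and 60 % (IVIg); one-sided alpha 5 % (z = 1.645); power 80 % (z = 0.842); dropout 20 %; 30 randomised per arm.

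**2. The plan's own figure.** With the pooled-variance formula and no continuity correction,

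n = [1.645·√(2·p̄(1−p̄)) + 0.842·√(p₁(1−p₁) + p₂(1−p₂))]² / (p₁ − p₂)²,

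with p₁ = 0.60, p₂ = 0.25 and p̄ = 0.425, gives n = 23.6, rounded up to 24 per arm. Then 24 / 0.80 = 30. The stated 24 and 30 reproduce. The design thus expects 24 of 30 per arm to be analysable.

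**3. What selective loss could do to the error rate.** Assume that the drug has no effect, that both arms have the same true response p, and that 6 of 30 leave each arm. If those who leave an arm are all nonresponders, the response rate among the remaining 24 is p / 0.80. If they leave at random, it stays at p. At p = 25 % the selected arm shows 0.25 / 0.80 = 31.25 %; at p = 40 % it shows 0.40 / 0.80 = 50 %. The probability that a one-sided uncorrected chi-square test (z > 1.645) favours IVIg was then found by exact binomial enumeration with 24 per arm:

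| Losses (6 of 30 per arm) | p = 25 % | p = 40 % |
|---|---|---|
| Random in both arms | 4.9 % | 5.2 % |
| IVIg nonresponders; placebo random | 11.8 % | 18.3 % |
| Nonresponders in both arms | 4.8 % | 5.6 % |
| Placebo nonresponders; IVIg random | 1.6 % | 1.1 % |

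With 3 of 30 lost per arm (27 analysed, selected arm at p / 0.90), IVIg-side selection gives 8.1 % and 9.5 %, and placebo-side selection gives 3.2 % and 2.5 %.

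**4. Power if ITT becomes primary.** Take 30 per arm, one-sided 5 %, with a proportion d of each arm dropping out and all dropouts counted as nonresponders. The rates become 0.25(1−d) and 0.60(1−d).

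| d | Rates | Power at 30 per arm | n per arm for 80 % |
|---|---|---|---|
| 0 | 25 % v 60 % | 88 % | 24 |
| 10 % | 22.5 % v 54 % | 82 % | 29 |
| 20 % | 20 % v 48 % | 75 % | 35 |

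At the planned 20 % dropout, the last row is a worst case. The article's ITT rule carries forward the last value of those who reach week 6, so some dropouts can still count as responders.

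**The case against.** The strongest objection is that the article never defines the per-protocol set. The full protocol or analysis plan may define it narrowly, and with multiple imputation and Kaplan-Meier curves also named, it is not fixed that every dropout leaves the comparison. This stands against any statement that particular patients will be excluded. The compliance text only asks for reasons to be recorded, and the analgesic condition sits in an eligibility criterion, not in a rule for the analysis set. It does not answer the main point, because choosing a per-protocol set as primary is a stated decision.

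A reader might infer that the choice inflates the result in favour of IVIg. The documents do not support that. Losing IVIg nonresponders inflates the result, but losing placebo nonresponders does the opposite. Placebo patients who change analgesics because pain persists would probably be nonresponders, and removing them would work against IVIg.

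There is also mitigation. Patients and investigators are blinded, which limits biased decisions about exclusion but does not stop a poorly tolerated drug from causing drop-out. ITT analyses with explicit dropout rules are prespecified. The Background section calls the trial a pilot study. These points lessen the risk. They do not make the ITT result the one that decides.

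The enumeration also has limits. It treats the dropout allowance as the per-protocol exclusion rate, and it uses the chi-square test of the sample size section although the primary analysis names the log-rank test.

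**Conclusion.** The point holds: the primary superiority comparison is placed in a population selected after randomisation, and nothing in the article makes ITT primary or co-primary. The abstract's reference to the first randomisation names no analysis set. The consequence is that the one-sided 5 % error rate is not assured. It is not shown that the rate is raised.

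Under the stated assumptions the range across scenarios is about 1 to 18 %, against a nominal 5 %. These are illustrations and not forecasts; the article gives no basis for choosing among them. The statement that the per-protocol and ITT comparison gives a good impression of the bias is stronger than the two analyses can support.

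**What to change.** - Make the primary comparison ITT: all randomised patients, as allocated, with one stated rule for missing response. The week 6 rule already written for the ITT sensitivity analysis (carry forward after week 6, nonresponder before) would serve as an example.
- Keep the per-protocol analysis as supportive.
- Remove or soften the statements that comparing the two analyses shows the bias and gives the true effect.
- Restate the power for the ITT analysis under the chosen dropout rule.

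The cost is wording and the power statement; no new data collection is needed. At 30 per arm the power is at or above the planned 80 % if all patients are assessed or if 10 % drop out as nonresponders. In the worst case of 20 % it is 75 %, and holding 80 % in that case would take 35 per arm. The sponsor should either accept and state the lower figure or revisit the number.

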**Fig. 1 Fig1:**
[figure not shown]
Schematic diagram representing overall study design and study visits Legend: IVIg = intravenous immunoglobulin, red triangles represent the treatment visits. The first treatment visit is spread out over 2-4 consecutive days, treatment visit 2-4 will consist of 1-2 consecutive days

In brief, after a screening period of ≤ 10 days, eligible subjects are randomized to receive either IVIg at an uploading dose of 2 g/kg body weight (bw), ideally over 2–4 (consecutive) days, or a matching placebo. Thereafter, a study drug infusion is administered every 3 weeks at a dose of 1 g/kg bw, given over 1–2 (consecutive) days for a total of three additional infusions following baseline. The subjects’ pain is measured using Pain Intensity Numerical Rating Scale (PI-NRS) at baseline and at each study visit scheduled every 3 weeks for 12 weeks. Pain is also assessed twice a day (daytime and nocturnal pain, through PI-NRS) on 2 days each week (Monday and Friday). A responder is defined as a ≥ 1-point improvement on the mean weakly peak pain using the PI-NRS relative to baseline. Patients who show an improvement and complete the 12 weeks of study treatment will be followed during a 3-month-extension phase to determine the long-term effect of the received therapy on pain alleviation.

The study is placebo-controlled because in previous analgesic trials a placebo effect of 7-37 % has been shown [32]. To make sure IVIg has a factual effect on pain reduction, a placebo-controlled design is necessary to exclude the placebo effect of this treatment on the patients. In addition, patients are allowed to use pain medication that not has been changed in the 30 days prior to randomization. As a result, in case the patient receives a placebo, the treatment does not differ from the situation before participating in the study.

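### The primary responder test is valid but leaves out baseline pain; adding it as a covariate is a low-cost improvement worth roughly 0 to 9 points of power, and it repairs no error

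*Protocol article*

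**What the plan says.** Under Type of analysis, the protocol article compares the proportion of responders in the per-protocol population. A responder has a fall of at least 1 point in mean weekly peak pain "during the 12-week treatment period after first study drug infusion compared to baseline, using Kaplan-Meier curves (log rank test"). No covariate or stratification factor is named, and Randomization and blinding describes no stratification by pain.

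The same section analyses the secondary efficacy variables by "analyses of covariance (ANCOVAs) with the baseline measurement as the covariate". Study design has pain rated on the "Pain Intensity Numerical Rating Scale (PI-NRS) at baseline and at each study visit scheduled every 3 weeks for 12 weeks", so the covariate is already in the data. Table 1, however, marks the PI-NRS at screening and not at week 0. It is therefore unclear whether the baseline is the screening value or a later one.

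Sample size assumes 25 % and 60 % response ("we assume a response rate of approximately 25 % in the placebo-treated group"; "we assume a response rate of approximately 60 % based on the IMMPACT criteria") and concludes that "a sample size of 24 patients per treatment group would be required to show efficacy with 80 % power", at a one-sided 5 % level with a chi-square test. This becomes 30 per arm after dropout.

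**The concern.** Response is baseline minus follow-up, cut at 1 point. Unless the two scores are almost perfectly correlated, a patient whose baseline is high, partly by chance, reaches the cut more easily. A test that ignores baseline leaves this variation in the noise. With about 30 per arm and no described stratification, the arms may also start at somewhat different pain levels, which shifts the responder curves apart from any drug effect. The protocol adjusts the secondary outcomes for baseline but not the primary one, and gives no reason. At stake are some power and how securely a single result can be read.

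**Working it through.** **Inputs from the protocol.** 25 % and 60 % response, one-sided 5 %, 80 % power, 24 evaluable and 30 enrolled per arm (Sample size); SD about 2, implied there by taking 1 point as half an SD; entry pain of 5 or more (Inclusion criteria).

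**Assumptions, not in the protocol.** Mean baseline 7, normal scores, baseline/follow-up correlation ρ from 0.3 to 0.9, no treatment-by-baseline interaction.

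**1. The plan's own figure.** With p̄ = 0.425,

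n = [1.645·√(2·0.425·0.575) + 0.8416·√(0.25·0.75 + 0.60·0.40)]² / 0.35² = (1.150 + 0.550)² / 0.1225 = 23.6, so 24 per arm; 24/0.80 = 30.

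Power = Φ[(0.35·√n − 1.150)/0.6538]: 80.6 % at 24 per arm and 88.0 % at 30.

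For the log-rank test (Schoenfeld), HR = ln 0.40 / ln 0.75 = 3.185. Expected events are 24 × 0.85 = 20.4, and power is Φ(√(20.4/4)·ln 3.185 − 1.645) = 83.4 %. With 25.5 events (30 per arm) it is 90.0 %. The design reaches its target without adjustment.

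**2. Link between baseline and change.** With equal SDs, the squared correlation of baseline with change is (1 − ρ)/2: 0.35, 0.25, 0.15 and 0.05 at ρ = 0.3, 0.5, 0.7 and 0.9. Limiting baseline to 5–10 cuts its SD from 2 to about 1.29 and these values to about 0.18, 0.12, 0.07 and 0.02. The direction follows from the endpoint's definition; the strength is unknown.

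**3. Power gain.**

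(a) Shortcut, replacing n by n/(1 − R²), 24 per arm: R² 0.05 gives 82.4 % (+1.8 points), 0.15 gives 86.1 % (+5.5), 0.25 gives 89.8 % (+9.2). At 30 per arm, R² 0.15 to 0.25 gives +4.3 to +6.9.

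(b) Simulated log-rank against baseline-adjusted Cox, 24 per arm, by HR per SD of baseline: 1.22, +0.2; 1.42, +1.6; 1.65, +3.4; 2.0, +6.5; 2.46, +9.4.

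(c) Simulated single yes/no response, 24 per arm, chi-square against adjusted logistic model:

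| ρ | Baseline 5–10 | No entry limit |
|---|---|---|
| 0.3 | 82.1 → 85.7 % | 81.7 → 89.1 % |
| 0.5 | 81.9 → 83.8 % | 81.9 → 86.6 % |
| 0.7 | 82.1 → 82.9 % | 82.0 → 84.8 % |
| 0.9 | 81.8 → 81.7 % | 81.5 → 81.7 % |

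(d) Simulated first 1-point drop over four visits, 24 per arm, size-corrected, log-rank against adjusted test. With no entry limit: 81 v 92 % at ρ 0.3, 81 v 87 % at 0.5, 81 v 84 % at 0.7. With the screening value limited to 5–10 as baseline: 85 v 88 % at 0.3 and 81 v 85 % at 0.5. A further simulation gave about 1 to 6 points without the limit and −1 to 3 with it. The only settings clearly above 9 points have ρ = 0.3, the weakest correlation tried.

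**4. Chance imbalance.** The SE of the between-arm baseline difference is √(2/30) = 0.26 SD: about 0.5 point at SD 2, or 0.3 point at SD 1.29. A difference beyond half an SD in either direction has probability 5.3 % at 30 per arm and 8.3 % at 24. In simulations with no drug effect and 30 per arm, among trials where IVIg started at least one SE higher, the one-sided 5 % log-rank test rejected in about 8–18 %, against about 3–8 % with adjustment. Over all randomisations the log-rank test rejected in 3.4–5.3 %.

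**The case against.** The strongest reply is that nothing here is wrong. An unadjusted log-rank test is valid in a randomised trial, the trial was sized for an unadjusted test, and it reaches its target. ANCOVA for continuous change and a log-rank test for response are ordinary choices for different kinds of endpoint. The plan already provides baseline-adjusted results for daily, nocturnal and average pain, and an adjusted supportive responder analysis may sit in an analysis plan that is not shown. A Cox model brings a proportional-hazards assumption and a conditional effect measure, and its test ran at 5.1–6.5 % for a nominal 5 % in simulation.

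Most of this stands, and it sets the weight of the point. It does not remove it: the article itself names the primary test, and the adjusted pain results belong to secondary outcomes.

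Three stronger readings are tempting and are not supported:

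- A reader might infer that the trial forfeits a definite 5 to 9 points. That needs R² of about 0.15 to 0.25 in the shortcut, or an HR of about 1.8 to 2.4 per SD of baseline. The protocol gives no such figure, and the entry rule may weaken the association.
- A reader might infer that chance imbalance biases the test or inflates its error rate. The raised rejection rates in step 4 apply only to trials selected for an imbalance favouring IVIg; those tilted the other way reject less often.
- A reader might infer that adjusting the secondary outcomes alone is a contradiction. It is an unexplained difference in approach.

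**Conclusion.** The primary test is valid, and the stated sample size and power are reproduced. Leaving baseline out is an efficiency choice that could cheaply be improved.

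The gain is roughly 0 to 9 points of power at 24 per arm. It is likely about 0 to 4 points if the baseline is the screening value held to 5 or more. That limit is itself uncertain, because entry may instead rest on the first question of the NPS and a later baseline would be less restricted. The range rests on the assumed mean, SD, correlation and absence of interaction; the documents cannot narrow it.

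The second benefit is a safer reading of the one trial that will be run, should the arms differ at baseline. The statement that the unadjusted test keeps its level holds over repeated randomisation, and in the per-protocol set it also presumes that exclusions do not depend on arm.

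**What to change.** In Type of analysis, prespecify the primary test of time to response with treatment as factor and baseline mean weekly peak PI-NRS as a continuous covariate. Use a discrete-time model over the visits, or a Cox model with a tie method suited to so few visits. State which measurement is the baseline. If a test without a regression model is preferred, a log-rank test stratified by baseline pain is the alternative. With tertiles it recovered about half of the gain in simulation (at ρ = 0.5: log-rank 81–84 %, stratified 85–87 %, adjusted 88–90 %).

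Keep the Kaplan-Meier curves and the unadjusted responder proportions beside the adjusted result, and the unadjusted log-rank test as sensitivity analysis.

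The cost is a short change of wording, with no new data or patients. There are two downsides. The hazard ratio becomes conditional on baseline pain, which is why the raw proportions must stay. The model test's level at this sample size needs checking, for example by a re-randomisation p-value. The choice is credible only if fixed before unblinding; Trial status still places recruitment ahead.

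### The difference between the per-protocol and ITT results is not a measure of bias, and agreement between them does not show that drop-out did no harm

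*Protocol article*

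**What the plan says.** Under Type of analysis, the primary comparison of responders is made in the per-protocol population. The ITT analyses are sensitivity analyses with a two-part drop-out rule. For early leavers: "A subject dropping out before the week 6 PI-NRS assessment or any subject with no baseline PI-NRS will be counted as a nonresponder", whatever their last score was. Patients who leave with at least the week 6 assessment have their last mean weekly peak pain carried forward. A further sentence says that missing values will be multiply imputed, without saying how this fits with the two rules.

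The section then interprets the comparison: "The differences between the per-protocol analyses and the ITT analyses will give a good impression of the bias that might occur in the study". It adds that by comparing the two the investigators "can investigate the true effect of IVIg in the most reliable way".

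Under Sample size, the planned rates are given as "we assume a response rate of approximately 25 % in the placebo-treated group" and "In the IVIg treated group, we assume a response rate of approximately 60" %. Drop-out of about 20 % raises 24 to 30 per group.

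**The concern.** A gap between two analysis sets can measure bias only if it moves with the bias. The bias at issue is the distance between the per-protocol result and the result that would have been seen had every randomised patient been followed. It depends on how the drop-outs would have fared. If the ITT rule assigns those patients a fixed outcome, the gap cannot respond to that.

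The drop-out allowance implies about 6 patients per arm, so 12 of 60. With a per-protocol primary analysis in a trial of this size, a small gap could be taken as evidence that drop-out did not matter, and a large one as evidence that it did. Neither would follow.

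**Working it through.** **Inputs.** From Sample size: 25 % and 60 % response, one-sided alpha 5 %, 80 % power, chi-square test, 20 % drop-out. From Type of analysis: the two-part ITT rule. Assumptions: per-protocol means completers. The split of drop-outs before and after week 6 is not given, so I range it from all early to all late.

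**The plan's own figure.** The pooled two-proportion formula without continuity correction gives 23.6, so 24 per group (power 80.6 %). Then 24/(1 − 0.20) = 30. Both stated figures reproduce.

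**Drop-outs before week 6.** Let p be the per-protocol response rate and d the early drop-out fraction, with T for IVIg and C for placebo. Each arm's ITT rate is (1 − d)p, so

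gap = (pT − pC) − [(1 − dT)pT − (1 − dC)pC] = dT·pT − dC·pC.

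No term describes the drop-outs' own outcomes. With p = 0.60 and 0.25:

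| Early drop-out, IVIg / placebo | Per-protocol difference | ITT difference | Gap |
|---|---|---|---|
| 20 % / 20 % | 0.35 | 0.48 − 0.20 = 0.28 | 0.070 |
| 10 % / 10 % | 0.35 | 0.54 − 0.225 = 0.315 | 0.035 |
| 30 % / 10 % | 0.35 | 0.42 − 0.225 = 0.195 | 0.155 |
| 10 % / 30 % | 0.35 | 0.54 − 0.175 = 0.365 | −0.015 |

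If drop-out is random, the per-protocol result is unbiased in every row, yet the gap runs from −1.5 to 15.5 points.

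Now hold drop-out at 20 % per arm and let q be the unseen response rate among drop-outs. The all-randomised difference is 0.28 + 0.20(qT − qC).

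- qT = 0.60, qC = 0.25 (random drop-out): 0.35, so the per-protocol bias is 0.
- qT = 0, qC = 1: 0.08, bias +0.27.
- qT = 1, qC = 0: 0.48, bias −0.13.

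The gap is 7 points in all three. The last two are extreme bounds, not forecasts.

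**Drop-outs at week 6 or later.** Let r be the carried-forward response rate. With 20 % late drop-out per arm,

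gap = 0.20(0.60 − rT) − 0.20(0.25 − rC) = 0.07 − 0.20(rT − rC).

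This is 0 if late drop-outs respond like completers, 12 points at 0 % v 25 %, 17 points at 0 % v 50 %, and lies between −13 and +27 points at the limits. Here the gap does depend on observed data. With half the drop-outs early and half late, the limits are −3 and +17 points.

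**Agreement without security.** Take 6 early drop-outs per arm and one-sided pooled chi-square tests.

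| Comparison | Counts | p |
|---|---|---|
| Per-protocol | 14/24 v 6/24 | 0.010 |
| ITT, drop-outs as nonresponders | 14/30 v 6/30 | 0.014 |
| One placebo and no IVIg drop-out a responder | 14/30 v 7/30 | 0.029 |
| Two placebo and no IVIg drop-outs responders | 14/30 v 8/30 | 0.054 |
| Three placebo and no IVIg drop-outs responders | 14/30 v 9/30 | 0.092 |

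Of the 7 × 7 = 49 combinations of responders among the drop-outs, 15 lose significance. They are exactly those with at least two more responders among placebo than among IVIg drop-outs (5 + 4 + 3 + 2 + 1 = 15). The cells are not equally likely. If drop-outs respond independently at their arm's completer rates (14/24 and 6/24), the 15 cells together have probability of about 1.7 %. If both arms' drop-outs respond at 25 %, it is about 15.5 %.

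**The case against.** A reader might infer that the gap is set by drop-out alone and tells nothing about bias. The documents do not support that. The nonresponder rule covers only patients who leave before week 6 or have no baseline score. Later drop-outs enter with observed values, so the gap then says something about the effect of excluding them, provided carry-forward is acceptable. Even for early drop-outs the response rates enter as well as the fractions. If multiple imputation produced the ITT result, the identity above would fail and the gap would rest on the imputation model. If patients with other protocol deviations are also excluded from the per-protocol set, they would move the gap through their observed outcomes.

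A reader might also infer that this comparison is the plan's only robustness check, or that it decides whether a result is declared robust. Neither is stated. The section also lists 2-point responder analyses in both populations, the ITT one with a different missing-data rule, and it names multiple imputation. It gives no threshold or decision rule.

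Finally, the worked case uses the chi-square test of the sample-size section, whereas the primary comparison is specified as Kaplan-Meier with a log-rank test. Counting 15 of 49 cells without weighing them would overstate the fragility.

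All of this stands and limits the point. None of it makes the two sentences true. A fuller analysis plan could add analyses, but it could not turn the gap into a measure of bias.

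**Conclusion.** The point holds in limited form. Reading the per-protocol/ITT difference as bias, and the comparison as the most reliable route to the true effect, is not valid. For early drop-outs under the nonresponder rule the gap is mechanical: 7 points on the plan's own figures, whether the per-protocol bias is +27, 0 or −13 points. For later drop-outs it is informative only as far as carry-forward is believed, and under imputation only as far as the model is. Agreement of the two analyses therefore does not show absence of bias. How far it misleads depends on the unstated early/late split and on how plausible an excess of responders among placebo drop-outs is. The algebra rests on per-protocol meaning completers, and the p-values on the chi-square test. The planned sample size is not affected.

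**What to change.** Delete the two sentences, or reword them to say that the per-protocol and ITT results will be reported side by side and that their difference is not an estimate of bias or of the true effect.

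Add a tipping-point analysis on all randomised patients. Vary the number of responders among drop-outs with unobserved week 12 outcome from none to all, separately by arm. Recompute the responder difference and test for each combination. Report where the conclusion changes and discuss how plausible those combinations are, rather than only counting them.

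The cost is one extra table and the loss of a reassuring statement. No new data or patients are needed.
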